At present, pharmacologic approaches are not the answer. Despite the substantial improvement in supportive critical care that has occurred over time, there has not been seminal advances in addressing the central dysregulated inflammation ultimately causing the organ damage that kills or maims patients with severe sepsis. Attempts to derive pharmacologic therapies for combating post-infective inflammation have proved to be incredibly expensive and frustrating, with hundreds of failed anti-mediator trials having been conducted without evidence of significantly improved patient outcomes [25, 26].

A critical nuance to consider in understanding surgical source control is that the van Ruler RCT did not utilize a contemporary “open abdomen” (OA) approach in either arms and that the abdominal fascia was formally closed in both. Increasingly, the OA is being recommended as an attractive option to provide better control of intraperitoneal contamination. Now, this approach is perceived to be a safer option than in previous decades due to the development of advanced temporary abdominal closure (TAC) devices, that offer greater safety in protecting the viscera, and their potentially profound benefits in ameliorating the propagation of inflammatory bio-mediators in SCIAS [27–29].

The use of the OA for non-trauma general surgery is increasingly being reported in uncontrolled series as a potentially beneficial option for patients with SCIAS [12, 20, 21, 30–32]. The use of the OA in severe sepsis may offer early identification and increased drainage of any residual infection, control any persistent source of infection, more effectively remove bio-mediator-rich peritoneal fluid, provide prophylaxis against development of the abdominal compartment syndrome, and allow for the safe deferral of gastrointestinal anastomoses and a safer exit at the index operation [12]. Compared to trauma patients, however, patients undergoing OA management for intra-abdominal sepsis have a greater risk of OA complications, including enteroatmospheric fistula (EAF) and intra-abdominal abscess formation, and a lower rate of primary fascial closure (i.e., fascia-to-fascia closure within the index hospitalization) [12, 13, 33–35].

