Although case series reporting the use of the OA after non-trauma laparotomies have been reported, there are no other contemporary randomized studies to address this critical issue. There has only been one other RCT conducted prior to 2006 that randomized patients to a closed or open strategy, but the techniques of OA management used were inadequate as management of the OA has undergone dramatic improvements in technology and technique in recent years. Robledo and colleagues randomized patients with severe secondary peritonitis to an open or closed strategy after laparotomy, using a non-absorbable polypropylene (Marlex™) mesh in a interposed position between the open fascia, thus exposing the underlying bowel to great risk of enterocutaneous or enteroatmospheric fistula formation [36]. The study was stopped at the first interim analysis. Although the mortality difference between the two groups did not reach statistical significance, the risk of death was higher with the OA, interposed non-absorbable polypropylene mesh strategy [36].

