## Methods/design

### Objective/aims

The aim of the study is to test the null hypothesis that there will be no difference in survival when an OA management strategy administering ANPPT is utilized compared to a primary fascial closure strategy in patients with SCIAS. The study will be designed as a prospective, single-blinded, multi-center, international RCT. A SPIRIT diagram overview of the trial is presented in Table 1. The complete protocol is available at https://coolstudy.ca/.

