Emergency department	
Hospital ward	
Intensive care unit	
Vasopressors required prior to randomization—no. (%)	
Hours from sepsis diagnosis to laparotomy, median (IQR)	

^a^IQR interquartile range

^b^Septic shock as defined by SESPS-3 guidelines [7]

^c^WSESSS [8]

^d^CPIRO [43]

^e^*GCS* Glasgow Coma Score

^f^Acute Physiology And Chronic Health Evaluation II

^g^*INR* international normalized ratio

^h^*SOFA* Sequential Assessment of Organ Failure [110]

^i^Charlson Comorbidity Index [111]

^j^*PRBC* packed red blood cells

^k^*FFP* fresh frozen plasma

There will be a single interim analysis planned after the recruitment of 275 patients, which will analyze the difference in 90-day mortality between allocated therapies. The COOL investigators appreciate the general reluctance to stop randomized trials early due to the benefit and due to the frequent over-estimating of treatment effects [61–63]. Despite this, it is possible that the COOL trial will be great over-powered as although the sample size calculations are based on the best outcome data from randomized trials of NPPT, this is still inferential as there is no previous relevant data with which to accurately guide such calculations. Thus, if a profoundly significant difference is found (*p* < 0.01), the trial will be stopped; otherwise, it will continue to full recruitment (Fig. 2).

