## Conclusions

The COOL trial will be powered on demonstrating a mortality difference in this highly lethal and morbid condition to ensure critically ill patients are receiving the best care possible and not being harmed by inappropriate therapies based on opinion only. As this will constitute a major international collaborative, undertaking a number of secondary outcomes will be conducted that are expected to add to the basic and translational science of SCIAS.

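### The single interim look uses one direction-free p<0.01 threshold and orders continuation in every other case; a less stringent, non-binding harm review at the same look would be a cheap improvement

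*Protocol article*

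**What the plan says.** The Statistical analyses section of the protocol article fixes the interim rule in three parts.

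- **Timing:** "There will be a single interim analysis planned after the recruitment of 275 patients". The total is 550 (Discussion), so this is half of recruitment.
- **Endpoint:** the look is one "which will analyze the difference in 90-day mortality between allocated therapies". No other outcome is named for it.
- **Decision:** "if a profoundly significant difference is found (*p* < 0.01), the trial will be stopped; otherwise, it will continue to full recruitment".

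The section gives two reasons for so strict a threshold: early stopping for benefit tends to exaggerate effects, and the trial may prove over-powered. It does not mention stopping for harm. Sidedness is not stated. The Objective/aims section sets out to "test the null hypothesis that there will be no difference in survival", which points to a two-sided test.

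The abstract calls fascial closure the current standard of care, so OPEN is the experimental arm. The Background acknowledges its risks: compared with trauma patients, "patients undergoing OA management for intra-abdominal sepsis have a greater risk of OA complications, including enteroatmospheric fistula (EAF"), among others. Table 2 lists enterocutaneous fistula, abdominal compartment syndrome (ACS) or severe intra-abdominal hypertension (IAH), and intra-abdominal abscess as 30-day safety outcomes.

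**The concern.** The case for a very small p-value before stopping for benefit is familiar, and the article makes it. That case does not carry over to harm. If the experimental strategy appears to be killing more patients than the standard one, there is less reason to wait for equally strong evidence, because the practical response is to stop exposing patients and no claim of efficacy follows.

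Two features of the text matter together. The threshold has no direction, so the benefit bar is also the harm bar. And the word *otherwise* sends every result short of that bar to full recruitment. Read literally, a large but sub-threshold excess of OPEN deaths requires the second half of the trial to be recruited, whatever the complication counts show. This is a rule that the article states, not a detail it leaves out.

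**Working it through.** **Inputs**

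- Look at 275 patients: 137 CLOSED and 138 OPEN (Statistical analyses; allocation taken as 1:1 from the balanced blocks in Randomization).
- CLOSED mortality 33% and a 10-point design effect (Sample size calculations).
- Recruitment of 28 centres × 10 patients = 280 per year (Discussion).
- Assumptions: two-sided p<0.01 (critical z = 2.576), pooled two-proportion z-test, and 90-day status known for all 275.
- The harm scenario, 33% against 43%, is the design effect reversed. It is illustrative; the article does not expect it.

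**1. Observed excess needed to cross the threshold**

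z = d / √[2·p̄(1−p̄)/137.5], with p̄ = 0.33 + d/2.

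- d = 0.153: standard error 0.0592, z = 2.58, p just under 0.01.
- d = 0.100: standard error 0.0585, z = 1.71, two-sided p = 0.09.

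So about 15 points are needed. In counts, 45/137 CLOSED deaths (32.8%) against 66/138 OPEN deaths (47.8%) gives z = 2.53 and p = 0.011. The written rule would continue.

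**2. Chance of stopping for harm**

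Normal approximation at 33% against 43%: Φ[(0.10 − 2.576 × 0.0585)/0.0582] = Φ(−0.87) = 0.19.

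Exact binomial enumeration of 137 against 138, comparing the written rule with a one-sided p<0.05 harm trigger (z > 1.645, an observed excess of just under 10 points):

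| True OPEN mortality | Written rule stops for harm | One-sided p<0.05 trigger fires |
|---|---|---|
| 23% | <0.001% | 0.02% |
| 33% | 0.5% | 4.9% |
| 40% | 8.5% | 33% |
| 43% | 19.1% | 53.2% |
| 48% | 48.4% | 82.3% |

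At 43% the trial therefore continues 80.9% of the time. That becomes 84.2% with a continuity correction, 82.5% with Fisher's test, and 86.5% if only about 206 patients have 90-day data at the look. If p<0.01 were one-sided towards harm, it would be 73.3%.

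**3. Deaths at stake after the look**

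The 275th patient's 90-day status takes 90 days to mature. The article does not say that recruitment pauses meanwhile.

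- Enrolled during the wait: 280 × 90/365 ≈ 69.
- Still to recruit: 275 − 69 = 206, of whom 103 go to OPEN.
- Excess deaths at a true 10-point excess: 103 × 0.10 ≈ 10.
- Expected saving from the trigger: (0.532 − 0.191) × 10.3 ≈ 3.5, if every pause became a permanent stop.

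**4. Effect on the benefit analysis**

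A non-binding trigger in the harm direction cannot increase false claims of benefit. In 400,000 simulated trials at 33% against 23%, power for benefit was the same with and without it, at about 75%.

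**The case against.** **A symmetric rule is a legitimate choice.** It fits a null of no difference and the equipoise that the article claims, and it does stop the trial for harm at p<0.01. This stands: symmetry is neither an error nor a contradiction. What remains is that the stated rationale supports the threshold for benefit only.

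**The 81% largely reflects limited information at half the sample.** This also stands. A true 10-point benefit would continue about 77% of the time under the same rule. The figure describes how the rule behaves; it does not show a fault by itself.

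**Safety monitoring may be set out elsewhere.** The article points to a complete protocol that is not shown. A reader might infer that this is the trial's only safety rule, or that complications can never trigger action. The article cannot establish either. It does contain the *otherwise* clause, which would conflict with any harm rule held elsewhere.

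**Stronger support is tempting but not available:**

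- The Background reports of an earlier open-versus-closed trial that "The study was stopped at the first interim analysis", and adds: "Although the mortality difference between the two groups did not reach statistical significance, the risk of death was higher with the OA". A reader might take this as proof that the present rule would miss such a signal. The article gives no p-value, size of excess or reason for stopping, and it calls that trial's open technique inadequate.
- The Conclusions speak of patients "receiving the best care possible and not being harmed by inappropriate therapies based on opinion only". That describes the evidence the trial will give to practice and is not a monitoring commitment to participants.
- Counting all 275 remaining patients gives about 14 excess deaths (137 × 0.10), but this ignores enrolment during the 90-day wait.
- Nothing in the article shows that most monitors would act on a 10-point excess.

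**Conclusion.** The point holds as a worthwhile, inexpensive improvement in patient safety. It is not a must-fix error: neither the primary estimate nor its test is affected.

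The article asks for the same strength of evidence for harm as for benefit, gives reasons that cover only benefit, and orders continuation in all other cases. With CLOSED mortality at 33%, a two-sided test and complete 90-day data on 275 patients, the rule needs an observed OPEN excess of about 15 points. It stops for harm 8.5%, 19% or 48% of the time at true OPEN mortality of 40%, 43% or 48%. At the illustrative 10-point excess, about 10 excess deaths remain at stake after the look and a harm trigger might avert 3 to 4. That saving assumes that recruitment runs at the projected pace without pausing and that every triggered review ends in stopping, so it is an upper figure for that scenario. If the interim test were one-sided for benefit, harm would have no threshold in this rule at all.

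**What to change.** Amend the interim paragraph in Statistical analyses:

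- Keep p<0.01 for stopping for benefit.
- Replace the *otherwise* clause with wording that continuation is subject to independent review of the interim data, guided by a non-binding and less stringent harm criterion at the same look. One-sided p<0.05 for higher OPEN 90-day mortality is an example; the sponsor and monitors should set the level.
- State that the clause does not restrict safety review.
- Supply the reviewers with by-arm counts of fistula, ACS or severe IAH, and abscess, which are already collected.
- If the full protocol or a monitoring charter already contains a harm rule, reconcile this sentence with it.

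The cost is one paragraph, with no extra patients or looks. If the arms are truly equal, there is about a 5% chance of an unneeded review or pause. Type I error for benefit is not inflated.

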**Fig. 2 Fig2:**
[figure not shown]
Participant time line for COOL recruitment

### Ethical concerns

The Hippocratic Oath requires physicians to “consider for the benefit of my patients and abstain from whatever is deleterious and mischievous” and to “give no deadly medicine to any one if asked, nor suggest any such counsel”. Thus philosophically, as there is complete clinical equipoise concerning the treatment of SCIAS with or without the OA technique, the COOL investigators feel a moral imperative to provide the best evidence to counsel bedside critical care physicians and surgeons [64]. The COOL trial is currently approved by the Conjoint Research Ethics Board of the University of Calgary (REB-16-1588) to proceed with a delayed consent process given the time-sensitive critical nature of decision making. Research ethics will vary throughout the world, and it is anticipated that various local policies concerning community consent, waiver of consent, or informed consent of significant patient proxies will vary among the local approaches to ensure the COOL trial is performed to the highest ethical standards on a global basis. All participating institutions will thus be required to obtain ethical approval appropriate and applicable to their institutions.

## Discussion

The COOL trial has been designed to answer a critical clinical question that faces clinicians worldwide on a daily basis for which there is great clinical equipoise and potential severe consequences for patients in regard to potential poor outcomes [30, 42]. Thus, this question has been identified as one requiring urgent study by the most contemporary of international reviews [52]. Subsequently, the COOL trial has been endorsed by numerous scientific organizations with vested interest in the best care of the critically ill patient including the Abdominal Compartment Society, the World Society of Emergency Surgery, the Trauma Association of Canada, the Canadian Association of General Surgeons, and the Canadian Hernia Society. The trial design and vision follow directly from the preceding single-center study of differing modalities of APNPPT conducted at the Foothills Medical Centre, which noted a survival advantage associated with a more efficient APNPPT without being able to confirm a biological mechanism of such [41, 60]. When the peritoneal VAC investigators considered following up the pilot study and enrolling more patients in a multi-center fashion, it became apparent that any differing effectiveness of ANPPT techniques was not the most relevant question concerning the OA. With a dramatic evolution in resuscitation practices involving balanced resuscitation practices, more and more trauma patients who previously become so edematous required OA therapy, are no longer being crystalloid over-resuscitated, and can thus be primarily closed [65–67]. This dramatic change in the trauma care paradigm has justified questions regarding the whole premise of Damage Control Surgery for trauma [68] and justifies the randomized control trial of the practice in trauma patients [69].

As over-resuscitation becomes rare, and de-resuscitation becomes a focus [70], it is intuitive that there will be more abdomens in non-trauma intra-abdominal sepsis patients who may be technically closed without inducing intra-abdominal hypertension (IAH). However, although these abdomens *may* be closed, *should* they be closed? As has been recently emphasized, there are profound differences in the basic science of sepsis and traumatic injury [71], with the previously unifying concepts of non-infectious Systemic Inflammatory Response Syndrome (SIRS) being effectively discarded as a clinically helpful construct [7, 72, 73]. The one nebulous, poorly defined “holy-grail” of the optimal management of SCIAS is adequate “source control.” It is suggested that even if an abdomen can be physically closed, there may be an advantage to leaving it open to allow better drainage of intra-peritoneal contamination, a concept that is supported by remarkable animal lab data suggesting the ability of ANPPT to mitigate the elaboration of the inflammatory bio-mediator cascade [39, 40, 74]. Coupled with technical advances in ANPPT dressings that are safer to utilize and that increasingly protect the viscera, this appears an attractive option for the sickest IAS patients.

### The peritoneal cavity as a reservoir for systemic inflammation

There is a complex relationship between pressure, ischemia, and inflammation within the peritoneal cavity [10]. Independently, the damaged gut seems to act as a continued source of inflammation propagating SIRS and potentiating MODS [75–77]. Although extremely complicated, visceral ischemia further characteristically generates multiple immunological mediators with the pro-inflammatory cytokines tumor necrosis factor-alpha (TNF-α), and interleukin 6 (IL-6), as well as inhibitive cytokines such as interleukin 10 (IL-10) [78–81]. Post-operative complications are associated with increasing levels of systemic IL-6 and peritoneal TNF-α [80, 82]. Jansson and colleagues believe that peritoneal cytokines in humans respond more extensively compared to systemic cytokine and that a normal postoperative course is characterized by decreasing levels of peritoneal cytokines based on studies of both elective and emergency surgery [83]. Overall, the peritoneal cytokine response is much higher than the systemic response in peritonitis [81, 84–86]. Hendriks demonstrated that peritoneal cytokine levels (especially IL-6, TNF-α [87], and IL-10) were dramatically different in rats who either survived or succumbed to an intra-peritoneal sepsis model in the 24 h after cytokine determination [84]. Finally, the recent work suggests that blood filters designed to hemofiltrate blood endotoxins and cytokines may improve hemodynamics, organ dysfunction, and even mortality in the critically ill [88–91].

We believe that if it can be done safely, it is logical to attempt to remove intra-peritoneal bio-mediators to potentially ameliorate the local effects and to prevent them being absorbed systematically. Although early uncontrolled work suggested benefit to simple continuous peritoneal lavage after either gross peritoneal contamination in secondary peritonitis or in the setting of necrotizing pancreatitis [92, 93], more structured studies could not confirm such benefits [94–96]. Thereafter, work focused upon using hemofiltration to remove inflammatory mediators from the blood which has been associated with reduced elevations of inflammatory cytokines (as assessed by blood IL-6 levels), early improvements of hemodynamic state, and decreased lactate levels [97–99]. In an attempt to comprehensively increase efficiency, the potential utility of adding extra-corporeal mediator removal through hemofiltration in addition to continuous peritoneal lavage have been entertained and studied in early models [91].

ANNPT therapy may be a more direct and focused solution to this complicated problem and one that will be complementary to the other benefits of OA use in the sickest patients. Whether improved post-operative courses can be obtained through this relatively simpler approach of actively removing peritoneal cytokines with a more efficient and comprehensive VAC therapy in humans is therefore a stated secondary but important objective of the COOL-MAX arm of this trial.

Another potential benefit of ANPTT after severe infection may be the attendant decompression of the abdominal compartment and prevention of even modest degrees of IAH. Patients with intra-abdominal infections are at risk of elevated IAP both as a result of the primary intra-peritoneal disease, as any large fluid resuscitation often required to maintain organ perfusion [100–102]. Recent studies have demonstrated a high prevalence of IAH following aggressive resuscitation of septic patients. Intra-abdominal hypertension is present in as many as 80% of septic medical and surgical ICU patients [103, 104]. Reintam also reported that septic patients with IAH had a 50% rate of mortality compared to 19% without IAH, making IAH a significant marker for an increased risk of death [105]. Within our own institution, rates of IAH were over 87% of septic ICU patients, and further 61% of these patients had severe IAH at levels commensurate with ACS, despite the fact that IAP was only measured in 10% of the patients in whom guidelines recommend monitoring [106]. Although direct translation to humans is uncertain, even modest degrees of IAH (often clinically ignored) have been found to have profound far-reaching effects on propagating multiple organ failure in animals with ischemia/intra-peritoneal infections [107–109].

The investigators and the scientific community have extensively reviewed and critiqued the results of the preceding peritoneal VAC trial [90]. Methodologic concerns with the peritoneal VAC trial were that it enrolled quite heterogeneous patients with a wide range of ages and included traumatized patients with an exactly known time of injury and severe IAS patients in whom the timing of onset of severe disease was inexactly known. Thus, the COOL trial will focus on a less heterogeneous group of patients with intra-operatively confirmed SIAS in order to increase the signal to noise ratio. The Steering Group considers conducting the COOL trial to be a practical undertaking. With a projected total necessary recruitment of 550 patients and with an average institutional estimate of 10 such patients recruited per year, this projects to 28 actively engaged centers globally for 2 years. The initial expressed interest far exceeds this number of centers, and it is likely that many will be able to recruit many more than 10 per year. For example, at the Pilot Center, Foothills Hospital in Calgary, Canada, the group was extremely supportive with the similar recruitment process of the peritoneal VAC trial, in which out of 63 potentially eligible patients, 45 (71%) were recruited over 15 months [27], with reasons for non-recruitment including gynecological procedures and rescue laparotomies outside of a regular operating room.

